### Statistical methods

Data analyses will assess the *central* hypothesis that the combination of ergonomics and safety voice training will be more effective (as reflected in each dependent measure) than no training or either ergonomics training alone or safety voice training alone.

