## Methods/design

### Trial design

The SAVE project is a four arm, randomized-controlled study. The units of analysis will be individual apprentices. However, the units from which the apprentices will be recruited are apprenticeship training centers, with clusters of apprentices within centers assigned at random to one study arm, resulting in a cluster randomized-controlled trial design. Training centers will be randomly assigned to one of four groups: 1) ergonomic training alone, 2) safety voice training alone, 3) combined ergonomic and safety voice training, or 4) control group with no additional training intervention (Table 1).

**Table 1 Tab1:** Study design for Safety Voice for Ergonomics (SAVE) training intervention

		Safety voice training	
		Yes	No
Ergonomics training	Yes	All training	Ergonomic
	No	Safety voice	No training

An additional factor in the design will be repeated measurement of outcomes per apprentice on four occasions: 1) At baseline, 2) Post primary training for each group, 3) 6 months following primary training, and 4) 12 months following primary training. The resulting overall design will be a 2 x 2 x 4, Ergonomic Training by Safety Voice Training by Time of Measurement factorial design with repeated measures on the last factor and apprentices nested within training centers.

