#### General analytic approach

Preliminary analyses will include inspection of descriptive statistics and features of the data to determine whether data transformations for non-normal data are necessary. We will initially test whether baseline demographic characteristics and dependent variable scores are comparable between the four study groups using univariate analyses of variance or Wilcoxon rank-sum tests for continuous variables, and chi-square tests for categorical variables. Groups will be considered imbalanced on variables that differ at *p* < .10, and all such imbalanced baseline demographic factors will be included in primary analyses as covariates.

We intend to measure the dependent variables at four time points. Because repeated measurements on individual subjects tend to be correlated and, in some cases the number and intervals of time between observations may vary among subjects, and because the design uses clusters of apprentices within training programs, we will analyze each dependent measure with a general linear mixed model (GLMM) for clustered repeated measures data with modeling for 3 independent variables. These variables are 1) Ergonomic Training Group (Yes, No), 2) Safety Voice Training Group (Yes, No), and 3) Time of Assessment (baseline, post-primary training, and six and 12 months post-primary training) with covariates represented in the analyses as necessary, and between subject variability modeled as a random effect. GLMM will account for dependence in repeated measures and accommodate correlated errors, unequal correlations among time points, unbalanced data resulting from missing data points, and unequal intervals between testing occasions.

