Therefore, to assure that a test of means in the clustered design had sufficient power to establish superiority of any of the intervention groups over the control group, the sample size in standard power calculations was reduced by a factor of 2.4, resulting in a total study sample size of 40 for non-clustered power estimates, and a per-group sample size of 10. Effect sizes for determining power depended on information from a NIOSH systematic review examining the effectiveness of occupational safety and health training [31]. This review established that the across-study standardized mean difference between intervention and control groups post-training for the outcome measure of knowledge was 2.52, for attitudes and beliefs (e.g., self-efficacy, perceived risk, outcome expectations, behavioral intentions) was 0.84, and for behaviors (e.g., hazards and exposures under the worker’s control) was 1.09. Using the lower-bound effect size of 0.84, standard power calculations for a 2 x 2 x 4 design with repeated measures and a conservative estimate of correlation among repeated measures of 0.2, power (1 – β) to achieve statistical significance at a 2-sided type I error rate of .01 was 0.98 for the standard non-clustered design. Even with attrition averaging three apprentices per group (for a total sample size of 28), power would only be reduced to 0.96. In the clustered design, this would equate to a per-group sample size of 17. Given such robust estimates of power for a non-clustered design, we are confident that our clustered design with a sample size per group of 24 (with room for attrition to an n of 17) will have sufficient statistical power to detect significant differences among groups in statistical analyses that appropriately account for the effects of clustering. Power estimates were conducted with G*Power v. 3.1.7 [50].

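### The stated power of 0.98/0.96 does not cover combined training versus a single component, which the central hypothesis requires

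*Protocol article*

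**What the plan says.** All references are to the protocol article.

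- **Hypothesis.** Under Statistical methods, the analyses are to assess whether "the combination of ergonomics and safety voice training will be more effective (as reflected in each dependent measure) than no training"; the sentence extends the comparison to each single component: "than no training or either ergonomics training alone or safety voice training alone". The Abstract and the Background state the same hypothesis. It sets one arm against each of three others.
- **Design and model.** Trial design describes a "2 x 2 x 4, Ergonomic Training by Safety Voice Training by Time of Measurement factorial design with repeated measures on the last factor". General analytic approach lists the independent variables of the mixed model: "These variables are 1) Ergonomic Training Group (Yes, No), 2) Safety Voice Training Group (Yes, No), and 3) Time of Assessment". It does not say which term or contrast decides the central hypothesis.
- **Power.** Sample size and statistical power sets the aim as "sufficient power to establish superiority of any of the intervention groups over the control group". The effect size comes from a review that reported the "across-study standardized mean difference between intervention and control groups post-training". The calculation proceeds "Using the lower-bound effect size of 0.84" and reports that "power (1 – β) to achieve statistical significance at a 2-sided type I error rate of .01 was 0.98". With attrition to an effective total of 28 it gives 0.96. The section closes by expressing confidence that 24 per group, with room to fall to 17, is enough to detect differences among the groups.

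**The concern.** The comparisons that make this trial distinctive are trained versus trained: does adding safety voice to ergonomics, or ergonomics to safety voice, improve on the single component? The power section addresses trained versus untrained, then draws a conclusion about group differences in general. Two things change for the decisive comparisons. First, the likely effect is the increment over an active programme, and nothing in the article supports 0.84 for that. Second, only two of the four arms carry the comparison, so half of the effective sample drops out.

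If the figure is taken at face value, readers will believe that the trial is well placed to show that the combination beats its parts. A null result on combined versus single could then be read as evidence that combining adds nothing, when the trial had little chance of showing it.

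A related risk concerns interpretation. If combined and ergonomics alone do equally well and both beat the other two arms, the ergonomics main effect is real while the central hypothesis is false. If the two components add, the hypothesis is true while the interaction is zero. Neither term should stand in for the hypothesis.

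**Working it through.** **Inputs from Sample size and statistical power:** 12 centers, 3 per arm, mean 8 apprentices per center, 24 per arm, 96 in total; intracluster correlation 0.2; correlation among repeated measures 0.2; d = 0.84; two-sided alpha .01; four occasions (m = 4). **Assumptions added here:** f = d/2 for two equal groups, so f = 0.42; and, for sensitivity, an increment of d = 0.42 (f = 0.21).

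**1. Effective sample.** Design effect 1 + (8 − 1) × 0.2 = 2.4, and 96/2.4 = 40, or 10 per arm. Both match the article. The attrition case is 28, or 7 per arm.

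**2. The stated 0.98/0.96.** Noncentral F in the usual repeated-measures form. For time by a two-level factor, λ = N·m·f²/(1 − ρ) with 3 and 3(N − 2) df.
- N = 40: λ = 40 × 4 × 0.1764/0.8 = 35.28, power 0.996.
- N = 28: λ = 24.70, power 0.953.

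Other readings at N = 40 / N = 28:
- time main effect: 0.996 / 0.951
- time by four groups: 0.963 / 0.797
- two-level factor averaged over occasions: 0.925 / 0.762
- four groups averaged over occasions: 0.785 / 0.526

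Of these, only time by a two-level factor (20 versus 20) and the time effect come within two points of both stated figures. Both use every effective subject.

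**3. The same tests on the two arms that the hypothesis compares** (N = 20, or 14 after attrition).
- Time by group, d = 0.84, N = 20: λ = 20 × 4 × 0.1764/0.8 = 17.64, power 0.81.
- Four-occasion average: λ = N·m·f²/(1 + (m − 1)ρ) = 20 × 4 × 0.1764/1.6 = 8.82 on 1 and 18 df, power 0.55.
- One visit: λ = N·f² = 3.53 on 1 and 18 df, power 0.19.

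| Combined versus one component, alpha .01 | Time by group | Four-occasion average | One visit |
|---|---|---|---|
| d = 0.84, 10 versus 10 | 0.81 | 0.55 | 0.19 |
| d = 0.84, 7 versus 7 | 0.57 | 0.33 | 0.11 |
| d = 0.42 (assumed), 10 versus 10 | 0.16 | 0.11 | 0.04 |

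**4. Center-level degrees of freedom.** The table treats effective subjects as independent, which is favorable with 3 centers per arm. At one visit, SE = √(2 × 2.4/24) = 0.447. With 12 − 4 = 8 df, power is 0.14 at d = 0.84 and 0.035 at d = 0.42.

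**5. Main effect against simple effect.** Suppose ergonomics alone and combined both gain 0.84 and the other two arms gain 0. The combined-minus-ergonomics effect is then exactly 0. On the one-visit, 8-df basis of step 4, the ergonomics main effect (SE = √(2 × 2.4/48) = 0.316) is still significant at .01 with probability 0.33. On a more favorable basis (mean of three post-training visits minus baseline, variance (1 − r) × 4/3, stable center effects, 92 df) the probability is 0.91 at r = 0.2 and 0.99 at r = 0.5. On that same basis, combined versus single at 0.42 has power of only 0.12 to 0.20.

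**The case against.** The strongest reply concerns the analysis. A reader might infer that the factorial model cannot test the central hypothesis, or that the investigators would declare success on a main effect or look to the interaction. The article supports neither inference. It lists independent variables, not decisive tests. With the interactions that the 2 x 2 x 4 design implies, all four arm means at each visit can be estimated, and the three comparisons are linear combinations of the model terms. Under strict additivity the main effects equal the simple effects, so requiring both would test combined against each component, with more data. Contrasts and decision rules are commonly left to an analysis plan, which is not shown here; not naming them in an article is no error. All of this stands.

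A reader might also infer that power was computed strictly against control. That too is more than the text shows: the aim and the effect-size source are versus control, but 0.98 is labelled as a 2 x 2 x 4 calculation and comes closest to a pooled test.

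Finally, 0.42 is an assumption. True, but the shortfall does not depend on it: at the full 0.84, the two-arm figures are already well below 0.98.

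What the reply does not reach is the power section's own conclusion. It is printed text, and an unseen analysis plan would not correct it.

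**Conclusion.** The point holds for the power justification. The article claims enough power for differences among groups on the strength of 0.98/0.96, figures approached only by pooling all effective subjects and resting on an effect size for trained versus untrained. For combined versus one component, power at the full 0.84 is between 0.19 and 0.81 depending on the test, and between 0.11 and 0.57 with the stated attrition. If the increment is 0.42 it is between 0.04 and 0.16 without attrition. Inference on center-level degrees of freedom lowers it further, to 0.14 at one visit with d = 0.84.

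These values rest on the article's own correlations and alpha, on f = d/2, and on the reconstruction of the power test, which comes near the stated figures but does not match them exactly. Because the baseline occasion carries no training effect, the four-occasion average is, if anything, generous.

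On the analysis, the conclusion is limited: the model is usable, and the need is to tie the hypothesis to specific contrasts.

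**What to change.** 1. In Sample size and statistical power, give power for combined versus ergonomics alone and combined versus safety voice alone, on the two arms concerned, for a named test and time point. Show a range for the increment (for example 0.42 to 0.84), with and without the stated attrition, and say which degrees of freedom are used.
2. Remove the statement that 0.98/0.96 assures power for differences among groups, or confine it to the test to which those figures apply.
3. In Statistical methods, tie the central hypothesis to three contrasts from the mixed model with interactions: combined minus ergonomics, combined minus safety voice, and combined minus control. Say whether all three must succeed. If so, the error rate need not be split among the three.
4. State that neither a main effect nor the interaction, taken alone, confirms or refutes the central hypothesis.

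The cost is wording and a recalculation; the design and data collection are unchanged. The downside is that the published power for the central hypothesis becomes lower.

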#### General analytic approach

Preliminary analyses will include inspection of descriptive statistics and features of the data to determine whether data transformations for non-normal data are necessary. We will initially test whether baseline demographic characteristics and dependent variable scores are comparable between the four study groups using univariate analyses of variance or Wilcoxon rank-sum tests for continuous variables, and chi-square tests for categorical variables. Groups will be considered imbalanced on variables that differ at *p* < .10, and all such imbalanced baseline demographic factors will be included in primary analyses as covariates.

We intend to measure the dependent variables at four time points. Because repeated measurements on individual subjects tend to be correlated and, in some cases the number and intervals of time between observations may vary among subjects, and because the design uses clusters of apprentices within training programs, we will analyze each dependent measure with a general linear mixed model (GLMM) for clustered repeated measures data with modeling for 3 independent variables. These variables are 1) Ergonomic Training Group (Yes, No), 2) Safety Voice Training Group (Yes, No), and 3) Time of Assessment (baseline, post-primary training, and six and 12 months post-primary training) with covariates represented in the analyses as necessary, and between subject variability modeled as a random effect. GLMM will account for dependence in repeated measures and accommodate correlated errors, unequal correlations among time points, unbalanced data resulting from missing data points, and unequal intervals between testing occasions.

All analyses will be conducted based on the intention-to-treat principle in which any participant randomized to a treatment group remains in it regardless of adherence to or completion of treatment. We will measure level of participation and conduct a sensitivity analysis that assesses the stability of the conclusions from the GLMM analyses against an available-case analysis that considers only data from fully-adherent participants in a General Linear Model (GLM) repeated measures analysis of variance. The planned analyses involve multiple comparisons, which increases the likelihood that any single outcome will be found to be statistically significant based on chance alone. In order to buffer against potential inflation of type I errors due to multiple tests being performed, we will employ a more stringent type I error criterion (*p* = .01) than the typical .05 criterion.

Therefore, to assure that a test of means in the clustered design had sufficient power to establish superiority of any of the intervention groups over the control group, the sample size in standard power calculations was reduced by a factor of 2.4, resulting in a total study sample size of 40 for non-clustered power estimates, and a per-group sample size of 10. Effect sizes for determining power depended on information from a NIOSH systematic review examining the effectiveness of occupational safety and health training [31]. This review established that the across-study standardized mean difference between intervention and control groups post-training for the outcome measure of knowledge was 2.52, for attitudes and beliefs (e.g., self-efficacy, perceived risk, outcome expectations, behavioral intentions) was 0.84, and for behaviors (e.g., hazards and exposures under the worker’s control) was 1.09. Using the lower-bound effect size of 0.84, standard power calculations for a 2 x 2 x 4 design with repeated measures and a conservative estimate of correlation among repeated measures of 0.2, power (1 – β) to achieve statistical significance at a 2-sided type I error rate of .01 was 0.98 for the standard non-clustered design. Even with attrition averaging three apprentices per group (for a total sample size of 28), power would only be reduced to 0.96. In the clustered design, this would equate to a per-group sample size of 17. Given such robust estimates of power for a non-clustered design, we are confident that our clustered design with a sample size per group of 24 (with room for attrition to an n of 17) will have sufficient statistical power to detect significant differences among groups in statistical analyses that appropriately account for the effects of clustering. Power estimates were conducted with G*Power v. 3.1.7 [50].

## Discussion

Masons have the highest rate of overexertion injuries among all construction trades, the highest rate of repetitive bending and twisting, and exceed the construction industry average for nonfatal injuries resulting in time away from work [3]. Ergonomic solutions are the primary method of reducing these exposures and resulting injuries; however, many construction workers lack knowledge about ergonomic principles and solutions, and how to responsibly broach these topics in the hierarchical construction culture. Masonry apprentices are an optimal population for receiving SAVE training as they embark on their careers. The knowledge and skills these workers gain can assist them throughout their careers to minimize the cumulative exposure that leads to MSDs and to lead the construction industry in proactively working more safely. The SAVE project develops and tests an innovative approach to ergonomics and safety voice training that currently does not exist in the masonry trade or the construction industry.

The major strengths of our study are the use of blended learning methods, and the engagement of masonry instructors and the Masonry r2p Partnership in the SAVE project to develop and broadly disseminate a relevant apprenticeship training program. Another strength is the use of a cluster-randomized controlled trial design to accommodate regional training center differences, as well as a repeated measures design to evaluate the change in knowledge, attitudes and beliefs, and behaviors of the apprentices over time. We expect to face challenges with implementing the SAVE program with the diverse training schedules.

We expect to face potential threats to validity due to loss of follow-up and contamination. However, our team has over 15 years of experience conducting ergonomic and intervention effectiveness research in the construction industry and will do our best to minimize these threats. Analyses will be conducted examining differences between those lost to follow-up and those remaining in the study to assist in assessing the extent to which participants may differ from the target population. The threat to validity from contamination (i.e., the unwanted adoption of the interventions by the referent group) is addressed by implementing a single intervention per cluster (training center). Since the interventions require an infrastructure under the control of the investigators, it is unlikely that participants will be able to adopt the intervention without explicit assistance by the research team, preventing meaningful contamination.

From this work, we will develop evidence-based ergonomics training that is integrated with current apprenticeship curricula and disseminated throughout the masonry industry in the United States. The SAVE project will provide innovative training to a new generation of skilled masonry workers who are better equipped with evidence-based strategies for protecting their musculoskeletal health by working more safely.

## Abbreviations

BAC: international Union of Bricklayers and allied craftworkers
FTE: full time equivalents
GLMM: general linear mixed model
GLM: general linear model
ICE: international Council of Employers of Bricklayers and allied craftworkers
IMI: international Masonry Institute
MSD: musculoskeletal disorder
NIOSH: national Institute for occupational Safety and Health
OSHA: occupational Safety and Health Administration
r2p: research to practice partnership
SAVE: Safety Voice for Ergonomics
SF-12v2®: short form-12 health survey version 2
US: United States
